### Detailed description of intervention and control groups

This study applies an ecological momentary intervention [42] and comprises four groups: a dyadic action control intervention group, an individual action control intervention group, and two different control groups (see below).

At baseline assessment (T1), all participants (i.e. target persons and partners of all groups) receive an information leaflet on the benefits of moderate-to-vigorous physical activity for health and weight management and the recommendations on physical activity of the Swiss Federal Office of Sports (BASPO). The recommendation in 2011, when this study was planned, was to engage at least 30 minutes in moderate-to-vigorous physical activity per day. Subsequently, they are asked to answer a short quiz in order to make sure they understand the relevant information included in the leaflet. Wrong answers to this quiz are discussed with participants in order to provide correct information. This comprises the BCT “information about health consequences” [26]. In the following 14 days, all participants receive a short text message (SMS) once every weekday between 9–12 a.m. and 2–5 p.m. on their study smartphone (content of this SMS differs for intervention and control groups as well as for target persons and partners, see below). The time of the day the SMS is sent is randomly chosen, but equal for all study participants regardless of group membership. Figure 2 displays the experimental design.

**Figure 2 Fig2:**
[figure not shown]
**Experimental design.** Note: Exp. group = experimental group; PA = physical activity.

#### Experimental group I: dyadic action control group

After completing the assessments at the baseline session, target persons and their partners are instructed to collaborately form behavioral intentions to increase the target person’s physical activity to the recommended levels (e.g., “get off the bus two stops earlier when going to work” or “take the bike instead of the car”). This is supervised by a trained interviewer in order to ensure the correctness of the behavioral intentions. In terms of BCTs this part of the intervention comprise goal setting (behavior) [26].

Partners are instructed to send daily standardized text messages aiming at increasing the target person’s physical activity-specific action control in personalized form (e.g., “Dear Peter, which of the planned activities have you already carried out today? Love, Regula”) on weekdays during the two weeks following baseline assessment. All action control messages were developed by the authors and reviewed with regard to their action control content by two external reviewers who are experts in the field. A full list of all ten messages can be found in the Additional file 1: Table S1. In terms of BCTs, the different messages target self-monitoring of behavior and discrepancy between current behavior and goal [26]. Moreover, some messages are simple reminders on the behavioral intentions, targeting the awareness of own standards. Partners are instructed to save the personalized text messages as drafts in their study smartphones at the baseline assessment under the supervision of the study interviewer, and receive a reminder text message from the study personnel every day instructing them to send the text message within an hour (and to fill in the diary at the end of the day). Target persons are not informed about the instructions given to the partner, and both partners are asked not to talk about the text messages during the ongoing diary phase.

Moreover, both target persons and partners are instructed not to delete any of these SMS from the smartphones as this will allow a control of the implementation of the study protocol by participants [43].

#### Experimental group II: individual action control group

After completing the assessments at the baseline session, target persons alone are instructed to form behavioral intentions to increase their physical activity to the recommended levels. This is supervised by a trained interviewer to ensure the correctness of the behavioral intentions. On weekdays during the two weeks following baseline assessment, the target persons receive a text message daily from the study personnel with the same physical activity-specific action control content as the experimental group I. Partners of the target persons in this condition receive a text message at the same time reminding them to complete the diary at the end of the day. Again, both target person and partners are instructed not to talk about the text messages and not to delete any of these SMS from the smartphones as this will allow a control of the implementation of the study protocol by participants [43].

#### Control group I: full diary version

Couples in control group I are not instructed to form any behavioral intentions, but also receive SMS (at the same time as all other participants) with the reminder to complete the end-of-day diary.

#### Control group II: diary without self-reported physical activity

Couples of this second control group receive the same instructions and reminder text messages as control group I participants. As completing a diary on self-reported physical activity might in itself trigger self-monitoring, albeit not as strongly as the two intervention groups, the second control group serves the purpose to control for this potential diary effect by only completing questions on social-cognitive variables, but not on self-reported physical activity. Thus, this group will rely on ambulatory momentary monitoring of physical activity by means of an accelerometer only.

### Measures

For all groups, the online questionnaire (T0) comprises measures on sociodemographics, habitual physical activity, current diseases and activity-related health risks, and participating couples’ relationships.

At baseline (T1) both partners complete a comprehensive questionnaire for baseline assessment on current physical activity, physical-activity specific HAPA-variables, social control and social support with regard to physical activity, indicators of relationship quality, indicators of well-being as well as control variables. Likewise, weight, height and waist, and hip circumference (to assess the waist-hip ratio) are objectively assessed from both partners. Moreover, an objective submaximal aerobic fitness test on a bicycle ergometer is conducted with the target person.

The subsequent daily diaries (D1_1 – D1_28) include short scales/single items on HAPA variables, social support, social control, relationship quality, indicators of subjective well-being and for all but the second control group participants, a self-report physical activity assessment. Moreover, during the 28-days diary phase, all participants (target persons and partners) wear triaxial accelerometers around the hip (GT3X+ monitor devices; ActiGraph, Pensacola FL).

At the first and second follow-up (T2 and T3), both partners again complete a comprehensive questionnaire comparable to the T1 questionnaire and weight, height and waist, and hip circumference (to assess the waist-hip ratio) are objectively assessed. Only at T3, the objective submaximal aerobic fitness-test on a bicycle ergometer is conducted again with the target person.

Right after the second follow-up, the second 14-days diary phase plus accelerometer-assessment of physical activity takes place in order to be able to have another objective assessment of physical activity plus the accompanying cognitions and feelings assessed in the diary. This diary phase is very similar to the first one, but without including an intervention component in the intervention groups.

### Statistical analyses

To test the central hypotheses for the intervention effects at the between-person level with the baseline and follow-up points of measurement, repeated measures ANOVAs will be conducted using SPSS. Mediator analyses for the intervention effects will be done by means of regression analyses (Preacher & Hayes, 2004, 2008). To analyze intervention effects at the between- and within-person level on a daily basis using the first diary phase, multilevel modeling will be used [44]. Frequency and duration of physical activity can be considered a count variable, thus, generalized linear mixed Poisson models with a logarithmic link function will used to analyze the data [45]. To test dyadic associations (e.g., during the diary phase), two-level longitudinal models will be fit.

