### Power analysis

Effect sizes of action control interventions are medium to large (e.g., *f*^2^ = .25 in the study of Scholz & Sniehotta [46]; *f*^2^ = .42 in the study of Schüz et al. [23], for the volitional group). Thus, the analyses for the intervention effects from baseline to the two follow-ups with an assumed small correlation among repeated measures of *r* = .2 due to the expected change across time, with a power of .80, an alpha level of .05, a medium effect size of *f*^2^ = .25, and four intervention groups requires a total sample size of *N* = 88 couples (analyses are powered for between-effects on the individual; G*Power Version 3.1.9.2, [47]). Although there is one study reporting an attrition rate of 52% after 6 months for participants of a weight loss intervention [48], many intervention trials targeting physical activity report attrition rates around 20% [50, 51] across 6 months to two years. Thus, we conservatively assume an attrition rate of 30%. This results in *N* = 116 (*n* = 29 per group) couples needed for appropriate powered analyses of the effect of the intervention across the three points of measurement.

For the analyses on the intraindividual level during the diary phase, it is not possible to run power analyses. This is due to the fact that these power calculations require detailed information on parameters from previous studies [49]. Because this study is the first to test effects of individual and dyadic action control on daily physical activity, this kind of power analysis cannot be reported. Therefore, this study will serve as a basis for future studies focusing on intraindividual associations of dyadic and individual action control interventions.

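### The central repeated measures ANOVA counts the pre-intervention T1 value as an outcome; at the plan's own r = .2, a T1-adjusted model of T2 and T3 roughly halves the variance of the follow-up group effect

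*Protocol article*

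**What the plan says.** The Statistical analyses section of the protocol article sets the method for the between-person test of the central hypotheses: "with the baseline and follow-up points of measurement, repeated measures ANOVAs will be conducted using SPSS". Baseline (T1) is thus one level of the repeated factor, along with T2 and T3. The same section plans multilevel models for the daily data of the first diary phase and Poisson mixed models for activity frequency and duration treated as counts. Neither is assigned to the T1/T2/T3 test.

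The Power analysis section sizes the trial for this ANOVA at 80% power and a 5% significance level. For the dependence between waves it takes "an assumed small correlation among repeated measures of *r* = .2 due to the expected change across time". For the effect size and the resulting number it gives "a medium effect size of *f*^2^ = .25, and four intervention groups requires a total sample size of *N* = 88 couples", and it notes that "analyses are powered for between-effects on the individual". On dropout it says "Thus, we conservatively assume an attrition rate of 30" percent, and arrives at 116 couples (29 per group), described as the "couples needed for appropriate powered analyses of the effect of the intervention across the three points of measurement".

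**The concern.** Allocation is random and T1 is measured before the intervention, so the groups do not differ at T1 in expectation. With T1 as an outcome level, the ANOVA can be read in two ways, and both lose precision when the correlation is low:

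- The between effect averages T1 into the outcome, so one third of the average carries no intervention effect.
- The group-by-time effect in essence compares follow-up with T1. At r = .2, subtracting T1 adds more noise than it removes.

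The second strand is missed waves. The repeated measures ANOVA in SPSS, as normally run, keeps only cases with T1, T2 and T3. A target person seen at T2 but not at T3 would leave the central test despite having outcome data. With 30% attrition expected, this could affect a sizeable share of the sample.

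The stake is precision in a trial whose Discussion calls recruitment very challenging and recommends attention to effect sizes. The data for a more precise estimate are already being collected.

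**Working it through.** **Inputs.** From Power analysis: k = 4 groups, m = 3 waves, r = .2, alpha .05, N = 88 before and 116 after attrition, 30% attrition. The effect size is printed as f² = .25; the stated N reproduces only with f = .25, so f = .25 is used below. From Randomization: equal allocation. Assumptions made here: unit SD, compound symmetry, no effect at T1, the same effect at T2 and T3. The unit is the target person, one per couple.

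**Step 1: the plan's own figure.** For the between effect, λ = N·m·f² / (1 + (m−1)r), with df (k−1, N−k).
- N = 88: λ = 88 × 3 × 0.0625 / 1.4 = 11.79, df (3, 84), power 0.81. The smallest N reaching 0.80 is 86; the next multiple of four is 88. The figure reproduces.
- 116 × 0.7 = 81.2, so about 81 completers. At N = 81: λ = 10.85, df (3, 77), power 0.775.

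**Step 2: variance of the follow-up group effect, per person, at r = .2.**
- ANOVA between effect: the three-wave mean has variance (1 + 2r)/3 = 0.467 but carries only 2/3 of the follow-up effect. Rescaled: 0.467 × (3/2)² = 1.05.
- Follow-up mean minus T1: (1 + r)/2 + 1 − 2r = 0.60 + 1 − 0.40 = 1.20.
- Follow-up mean, T1 ignored: (1 + r)/2 = 0.60.
- Follow-up mean adjusted for T1: (1 + r)/2 − r² = 0.60 − 0.04 = 0.56.

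Ratios: 0.56/1.05 = 0.53 and 0.56/1.20 = 0.47. A simulation (20,000 runs, 29 per arm) gave 0.54 and 0.47. Adjustment itself contributes only the step from 0.60 to 0.56 (about 7%); the rest comes from no longer averaging in or subtracting T1.

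**Step 3: dependence on r.**

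| r | between | change | T1 ignored | T1-adjusted | adj./between | adj./change |
|---|---|---|---|---|---|---|
| .1 | 0.90 | 1.35 | 0.55 | 0.54 | 0.60 | 0.40 |
| .2 | 1.05 | 1.20 | 0.60 | 0.56 | 0.53 | 0.47 |
| .5 | 1.50 | 0.75 | 0.75 | 0.50 | 0.33 | 0.67 |
| .7 | 1.80 | 0.45 | 0.85 | 0.36 | 0.20 | 0.80 |

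The adjusted analysis has the smallest variance in every row, but the two ratios move in opposite directions as r rises.

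**Step 4: power with 81 completers, if f = .25 holds at T2 and T3 only.** N·f² = 81 × 0.0625 = 5.06.
- Group by time: λ = 5.06 × (2/3)/(1 − .2) = 4.22, df (6, 154), power 0.27.
- Between effect: λ = 5.06/1.05 = 4.82, df (3, 77), power 0.41.
- Follow-up mean, T1 ignored: λ = 5.06/0.60 = 8.44, df (3, 77), power 0.66.
- T1-adjusted: λ = 5.06/0.56 = 9.04, df (3, 76), power 0.69.

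Under the plan's own input (f = .25 on the three-wave mean) the between test has 0.775. If that averaged effect comes from T2 and T3 alone, the adjusted analysis has 0.97.

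**Step 5: missed waves.** 116 − 81 = 35 couples lost. The article does not say how many of them would have T2. Variance of the averaged follow-up effect from the T1-adjusted mixed model, relative to the completer between effect:
- none of the 35 with T2: 0.53
- 17 with T2: 0.48
- all 35 with T2: 0.44

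For the T3 effect alone, the T2-only couples reduce the variance by less than 1% at r = .2.

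**The case against.** Several counter-arguments are fair, and most limit the point.

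- **Validity.** With complete data, a repeated measures ANOVA is a valid test in a randomised design. This stands: the issue is efficiency and use of partial data.
- **Case deletion.** A reader might infer that the plan orders incomplete couples to be dropped. It does not. Deletion is how the standard SPSS procedure works, and an article may leave missing-data rules to a fuller plan. Only the named method can be criticised.
- **Retention.** A reader might infer that a mixed model would rescue all 35 lost couples. It uses only those with at least one follow-up; those lost before T2 stay lost.
- **Bias.** Attrition that differs by arm is conceivable because the arms differ in partner involvement, but no figure in the article supports it. The mixed model itself assumes data missing at random, so dropout driven by unobserved failure to become active would remain a problem.
- **Power.** A reader might take 0.27 or 0.41 as the trial's power. Those values place f = .25 at T2 and T3 with nothing at T1, which is not the plan's parameterisation; the plan's input gives 0.775. Taking the printed f² = .25 literally (f = .5) with the same follow-up-only pattern gives 0.87 for group by time and 0.96 for the between effect. The printed effect size is a separate matter.
- **Scope.** Accelerometer wear starts the day after T1, and fitness is tested only at T1 and T3. One model cannot serve every outcome.

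What survives is that the article does fix the method and the role of T1, and that the adjusted analysis has the lower variance at every r shown.

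**Conclusion.** The point holds as a recommended improvement. It is not an error that invalidates the central test. At r = .2, with compound symmetry and an equal effect at T2 and T3, the planned analysis estimates the follow-up group effect with about 1.9 times (1.05/0.56, between effect) or 2.1 times (1.20/0.56, change from T1) the variance of the T1-adjusted follow-up mean. Any statement of the gain should name r and the comparator. Keeping T2-only couples adds a further gain for the averaged effect and almost none for T3 alone. The conclusion covers outcomes measured at T1, T2 and T3, such as questionnaire physical activity and BMI. Claims that the article prescribes completers only, or that attrition will bias the comparison, go beyond what it says.

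**What to change.** In Statistical analyses, for outcomes measured at T1, T2 and T3, replace the repeated measures ANOVA with a mixed model:

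- outcomes: T2 and T3
- fixed effects: group, time, group by time, and the T1 value as covariate
- unstructured covariance
- all randomised target persons with at least one follow-up, in their assigned group
- a count version where the outcome is analysed as a count

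Report the group effect at T2, at T3 and averaged. For aerobic fitness, analyse T3 adjusted for T1. State that the T1 adjustment does not apply to accelerometer activity. Keep the completer ANOVA as a sensitivity analysis.

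The cost is revised wording and a few lines of syntax in the same software, with no new data. The downsides are slightly more analysis work, reliance on a missing-at-random assumption, and no recovery of couples lost before T2.

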### Power analysis

Effect sizes of action control interventions are medium to large (e.g., *f*^2^ = .25 in the study of Scholz & Sniehotta [46]; *f*^2^ = .42 in the study of Schüz et al. [23], for the volitional group). Thus, the analyses for the intervention effects from baseline to the two follow-ups with an assumed small correlation among repeated measures of *r* = .2 due to the expected change across time, with a power of .80, an alpha level of .05, a medium effect size of *f*^2^ = .25, and four intervention groups requires a total sample size of *N* = 88 couples (analyses are powered for between-effects on the individual; G*Power Version 3.1.9.2, [47]). Although there is one study reporting an attrition rate of 52% after 6 months for participants of a weight loss intervention [48], many intervention trials targeting physical activity report attrition rates around 20% [50, 51] across 6 months to two years. Thus, we conservatively assume an attrition rate of 30%. This results in *N* = 116 (*n* = 29 per group) couples needed for appropriate powered analyses of the effect of the intervention across the three points of measurement.

For the analyses on the intraindividual level during the diary phase, it is not possible to run power analyses. This is due to the fact that these power calculations require detailed information on parameters from previous studies [49]. Because this study is the first to test effects of individual and dyadic action control on daily physical activity, this kind of power analysis cannot be reported. Therefore, this study will serve as a basis for future studies focusing on intraindividual associations of dyadic and individual action control interventions.

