**Longitudinal design.**

### Randomization

The randomization comprises on the one hand the randomization to one of the four groups (two control groups and two intervention groups) and on the other hand the gender-balanced randomization of the couple into a target person receiving the intervention and a partner condition. For this reason, blocking as means of restricted randomization is used. Within a block of eight participating couples, two couples each are assigned to one of the four groups, once the man and once the woman assigned as target person. Before the beginning of the study, a computerized random-number generator is used for sequence generation of blocks. This allocation sequence is generated by an assistant that is not part of the study team and concealed in a set of sealed, numbered envelopes, and thus remain unknown to any of the investigators until the group assignment. On the day of the baseline assessement (T1), the interviewer conducting the session opens the appropriate numbered envelope and prepares the study materials accordingly.

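### The stated 80% power belongs to the group effect averaged over baseline and both follow-ups; for f = .25 appearing after baseline, the planned ANOVA has about 44% (main effect) or 30% (group by time) at N = 88

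*Protocol article*

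**What the plan says.** The Power analysis section of the protocol article describes its target as "the analyses for the intervention effects from baseline to the two follow-ups with an assumed small correlation among repeated measures of" r = .2. The other settings are "with a power of .80", "an alpha level of .05" and "a medium effect size of *f*^2^ = .25, and four intervention groups". The result is 88 couples, with a note in brackets that the "analyses are powered for between-effects on the individual". After an allowance for 30% attrition the target becomes 116 couples, 29 per group, which the section calls enough to study "the effect of the intervention across the three points of measurement".

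The Statistical analyses section says that the central between-person hypotheses will be tested "with the baseline and follow-up points of measurement, repeated measures ANOVAs will be conducted using SPSS". Baseline is therefore one of the levels of time.

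Allocation is random in blocks of eight, in which "two couples each are assigned to one of the four groups". In both intervention groups the goal-setting step follows the T1 assessments, and the text messages come in the two weeks after baseline.

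**The concern.** In a repeated measures ANOVA, the between-subjects main effect compares group means averaged over all time points. T1 is measured before any group-specific intervention in randomised groups, so its expected group difference is zero. Including it in the average dilutes any effect that appears at T2 and T3. The section names one target, change from baseline to the follow-ups, but attaches to it the power of a different test.

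If the planning effect is f = .25 at the follow-ups, the ANOVA would miss it more often than not. A null result would nevertheless be read as coming from a trial with 80% power.

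**Working it through.** **Inputs.** From the Power analysis section: alpha .05, power .80, k = 4 groups, m = 3 measurements, r = .2, effect size printed as f² = .25, N = 88, attrition 30%, 116 recruited. From Randomization: equal allocation. Completers: 116 × 0.70 = 81.2, so 81.

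**Step 1. Reproduce N = 88.** For the between-factors test, λ = f²·N·m / (1 + (m − 1)r), with k − 1 and N − k degrees of freedom.

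- f = .25, N = 88: λ = .0625 × 88 × 3 / 1.4 = 11.79; power .814.
- f = .25, N = 84: λ = 11.25; power .792. So 88 is the smallest balanced N.

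Other settings do not give 88:

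| Setting | N for 80% |
|---|---|
| Between, m = 2, f = .25 | 112 |
| Between, m = 1, f = .25 | 180 |
| Group by time, m = 3, f = .25 entered directly | 64 |
| Between, m = 3, f = .50 (f² = .25 as printed) | 28 |

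The value entered was therefore f = .25, for the main effect over three measurements.

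**Step 2. Put a null baseline into that test.** Effects (0, f, f) at T1, T2 and T3 average to (2/3)f. With f = .25 this is .1667, and f² = .0278.

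- N = 88: λ = .0278 × 88 × 3 / 1.4 = 5.24; power .441.
- N = 81: λ = 4.82; power .407.
- N = 116 (no attrition): λ = 6.90; power .567.

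At N = 88 the test reaches 80% at an averaged f of .246, so the follow-up effect must be .246 × 3/2 = .37.

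**Step 3. Group by time under the same profile.** Here λ = N·Σ(d_t − d̄)² / (1 − r), with 6 and 168 degrees of freedom. For (0, f, f), the sum is (2/3)f². At N = 88: λ = 88 × .0625 × (2/3) / 0.8 = 4.58; power .297. A simulation of 40,000 trials gave .441 for the main effect and .30 for group by time.

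**Step 4. Role of r, at N = 88 and f = .25.**

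| r | Main effect, f = .25 at all three times | Main effect, null T1 | Group by time, null T1 |
|---|---|---|---|
| .2 | .81 | .44 | .30 |
| .5 | .65 | .32 | .47 |
| .7 | .56 | .27 | .73 |

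Of these values, r = .2 is the most favourable for the between test that was powered.

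**Step 5. Baseline-adjusted alternative.** For the mean of T2 and T3 adjusted for T1, the residual variance is v = (1 + r)/2 − r², and λ = N·f²/v with 3 and N − 5 degrees of freedom. At N = 81 and f = .25:

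- r = .2: v = .56, λ = 9.04, power .689.
- r = .5: v = .50, λ = 10.13, power .743.
- r = .7: v = .36, λ = 14.06, power .880.

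**Step 6. The printed label taken literally.** With f = .50 at both follow-ups and r = .2, the averaged f is .333. Power at N = 88 is then .975 for the main effect and .905 for group by time.

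**The case against.** The strongest reply is that the article prints f² = .25, not f = .25, and calls effects of this kind medium to large. If f = .50 is what the authors expect, even the diluted test has 97.5% power at N = 88, and the threshold of f = .37 (f² about .14) lies below both cited values, .25 and .42. This stands as a condition: the 44% applies only if f = .25 is the planning effect. It does not rescue the power statement, because f = .50 would require 28 couples. N = 88 shows which number was entered, but not which effect the authors believe in.

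A second reply is about scope, and it stands. Accelerometers are issued at T1 and recording starts the next day, so that main outcome has no baseline value to dilute the effect. The diary analyses use multilevel models, for which the article gives no power. Aerobic fitness is measured only at T1 and T3, so the three-visit figures do not describe it.

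Third, the article discloses that between-effects were powered, and its Discussion favours effect sizes over significance tests. This softens the harm of a null result but does not correct the stated 80%.

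On r, a reader might infer that r = .2 worsens the dilution, or that its justification is simply wrong. Neither holds. Power of the between test falls as r rises, so r = .2 helps it. A uniform shift over time leaves a correlation unchanged, but change that differs between persons can lower it, and the article does not say which it means.

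**Conclusion.** The concern holds in a limited form. The 80% at N = 88 is the power of the group main effect averaged over three visits with f = .25, not of an effect from baseline to the follow-ups. For outcomes measured at T1, T2 and T3, such as questionnaire physical activity and BMI, with f = .25 at both follow-ups, none at T1 and r = .2, the main-effect test has about 44% power at N = 88 (41% at 81 completers), and group by time has about 30% at N = 88. Neither is near 80%.

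A reader might conclude that the trial is underpowered for all its main outcomes, or that it must recruit the 188 analysed couples that the diluted main-effect test would need for 80%. The documents do not support that. Accelerometer activity is outside this calculation, the planning effect is ambiguous between f = .25 and f = .50, and adjusting for baseline recovers much of the loss with the couples already planned.

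**What to change.** 1. In Power analysis, correct the f/f² label and state which value is the planning effect.
2. In Statistical analyses, for outcomes measured at T1, T2 and T3, make the baseline-to-follow-up test the group comparison of the mean of T2 and T3 adjusted for T1.
3. In Power analysis, restate power for that test at 81 completers. With f = .25 it is about 69%, 74% and 88% for r = .2, .5 and .7. Note that r = .2 was the favourable choice for the between test.

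Items 2 and 3 belong together: printing 69% while keeping the repeated measures ANOVA would create a new mismatch. If the ANOVA is kept, print its own power instead: at N = 88, f = .25 and r = .2, about 44% for the main effect and 30% for group by time.

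The cost is a less favourable stated power and a small change to the analysis. No extra couples are needed.

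### The stated .80 power belongs to a group effect averaged over T1, T2 and T3; with no effect possible at T1 it needs f = .375 at both follow-ups, which the plan does not state

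*Protocol article*

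**What the plan says.** The Power analysis section describes its target as "the analyses for the intervention effects from baseline to the two follow-ups with an assumed small correlation among repeated measures". It specifies "with a power of .80", "an alpha level of .05", "an assumed small correlation among repeated measures of *r* = .2" and "a medium effect size of *f*^2^ = .25, and four intervention groups", and arrives at 88 couples, raised to 116 for attrition. A parenthesis then adds that "analyses are powered for between-effects on the individual". The same section says that the sample is meant to serve the analysis over three points of measurement.

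Under Statistical analyses, the central between-person hypotheses are to be tested as follows: "with the baseline and follow-up points of measurement, repeated measures ANOVAs will be conducted using SPSS". Baseline is thus one of the waves in the model.

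Two other sections fix what can be expected at T1. Under Randomization, couples are allocated at random: "Within a block of eight participating couples, two couples each are assigned to one of the four groups". In the descriptions of both experimental groups, intentions are formed only once the T1 assessments are done, and the text messages come in the two weeks after that.

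**The concern.** The paragraph describes one effect and sizes another. A change from baseline to follow-up that differs between groups is a group-by-time effect, or a baseline-adjusted difference at follow-up. The test sized is the main effect of group, which compares group means averaged over all waves. One of the three waves lies before the intervention, where randomisation makes the expected difference zero, so an effect that exists only at T2 and T3 is diluted by a third in that average.

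The paragraph does not say whether .25 is the effect at follow-up or the effect averaged over all waves, and it prints f² where the sample size implies f. A reader cannot tell which intervention effect the trial has .80 power to detect. Depending on the answer, the same 88 couples are either well short of .80 or comfortably above it. This is the only sample-size justification given for the central hypotheses.

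**Working it through.** **Inputs.** From Power analysis: alpha .05, four groups, r = .2, three waves (T1, T2, T3), N = 88, effect size .25 (printed as f²). From Randomization: equal allocation, so 22 couples per group.

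**Step 1: reproduce N = 88.** For the between-groups main effect in a repeated measures ANOVA with m waves, the noncentrality is λ = N·m·f² / (1 + (m − 1)r), with df = 3 and N − 4.

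- With f = .25: λ = 88 × 3 × .0625 / 1.4 = 11.79, df 3 and 84, power .81. The smallest N is 86, or 88 in equal groups. This matches the plan.
- With f² = .25 as printed (f = .5), the same test needs 28.
- Other options also miss 88: two waves give 112, four waves 76, the within-between interaction with f = .25 entered directly 64, the within factor 44, and a one-way comparison at one time 180 (f = .25) or 48 (f = .5).

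So the stated N comes from f = .25 and the main effect over three waves.

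**Step 2: set the T1 difference to zero.** If the effect is f at T2 and T3 and zero at T1, the wave-averaged effect is (0 + f + f)/3 = (2/3)f.

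- For f = .25: averaged f = .167; λ = 88 × 3 × .0278 / 1.4 = 5.24; power .44. A simulation of 20,000 trials gave .446.
- For f = .5: averaged f = .333; λ = 88 × 3 × .1111 / 1.4 = 20.95; power .975.
- To recover λ = 11.79, the follow-up effect must be .25 × 3/2 = .375, that is f² = .14.

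**Step 3: group-by-time, same pattern of means.** The effects 0, f, f have variance (2/9)f² around their mean, so the interaction effect is f_I² = (2/9)f², with λ = N·m·f_I² / (1 − r) and df 6 and 168.

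- For f = .25: f_I² = .0139; λ = 88 × 3 × .0139 / .8 = 4.58; power .30.
- For f = .5: λ = 4 × 4.58 = 18.33; power .90.

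**Step 4: baseline-adjusted comparison of the mean of T2 and T3.** The residual variance is (1 + .2)/2 − .2² = .56. For f = .25: λ = 88 × .0625 / .56 = 9.82, df 3 and 83, power .73.

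| Follow-up effect, zero at T1, N = 88, r = .2 | Main effect over T1–T3 | Group-by-time |
|---|---|---|
| f = .25 (f² = .0625) | .44 | .30 |
| f = .5 (f² = .25) | .975 | .90 |

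With f = .25 and all 116 couples complete, the two powers are .57 and .39. With 116 less 30% (about 81 couples), the main effect has .41.

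The results also depend on r. With f = .25 and r = .5, the group-by-time power at N = 88 is .47 instead of .30.

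**The case against.** The strongest reply is that the document prints f² = .25 and takes it from earlier studies reported with f² = .25 and .42. If that is the effect expected at both follow-ups, 88 couples give .975 on the sized test and .90 on group-by-time, even with nothing at T1. On the printed effect size there is no shortfall. This stands. It means that 44% and 30% cannot be called the trial's real power; they apply only if .25 is f, the reading that produced N = 88.

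A second reply is that the effect size in this test describes wave-averaged means, so the authors may have had f = .375 at follow-up in mind. That equals f² = .14, below both of the cited values. A reader might infer from the calculation that the plan assumed a group difference already at T1. The text does not say so, and a larger follow-up effect with zero at T1 gives the same .81. What remains is that the text states neither assumption.

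Third, the group-by-time figure depends on convention: with f = .25 entered directly as the interaction effect, 64 couples suffice and power at 88 is .94. That also stands, and it is another reason to define what .25 measures.

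Fourth, the dilution applies only to outcomes that have a T1 value. Accelerometer wear is described as starting with the diary phase on the day after baseline, so for that main outcome no T1 wave is described. Finally, the Discussion recommends looking at effect sizes rather than significance. That softens how a null result might be read, but it does not correct the stated power.

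**Conclusion.** The point holds in conditional form. The calculation reproduces, but for a main effect averaged over a pre-intervention wave and not for the change from baseline that the paragraph names. For outcomes measured at T1, .80 on the sized test requires f = .375 at both T2 and T3, and the protocol does not state this. With f = .25 at follow-up, power is about .44 for that test and .30 for group-by-time; with f² = .25 it is about .98 and .90. These values assume 88 complete couples, equal groups, a common correlation of .2, an equal effect at both follow-ups and none at T1.

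A reader might conclude that the trial simply has 44% power. The document does not support that, because its printed effect size leads to the opposite result. What it does show is that the printed effect size, the stated N and the described effect do not belong to one calculation.

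**What to change.** Rewrite the power paragraph:

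1. Correct the notation, stating whether .25 is f or f².
2. Name the effect that tests the intervention: group-by-time, or a baseline-adjusted comparison at follow-up. Do not use the main effect averaged over T1.
3. Set the expected T1 difference to zero, and restate the power for the named effect with the effect size assumed at T2 and T3 and the value of r. Alternatively, keep the existing calculation and say plainly that its .80 requires f = .375 at both follow-ups.

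The cost is one paragraph and, if .25 proves to be f, a less favourable stated power. No additional couples and no change to trial conduct are needed.
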